**Figure 3 fig3:**
[figure not shown]
Individual sketches (top) and results from intermediate group analyses (bottom) indicating recalled localization and extent of the body area affected by visceral (left) and somatic (right) pain stimulation experienced on study day 1.

#### Neuroendocrine and neurochemical variables

2.5.4.

As indicators of stress-related activation of the hypothalamus-pituitary–adrenal (HPA) axis and the sympathetic nervous system, respectively, saliva samples are collected for analyses of concentrations of cortisol and alpha-amylase activity. Sampling is accomplished immediately prior to and after each pain stimulation phase on both study days, in parallel to questionnaire assessment of the current emotional state with the State–Trait-Anxiety-Depression-Inventory [STADI, state version (62)]. Additional sampling is accomplished upon arrival on both study days.

Blood draws are accomplished only on study day 1 at three time points (i.e., prior to the *Experience Phase*, after the *Experience Phase*, after the *Test-1 Phase*), enabling later exploratory analyses of ß-endorphin and cholecystokinin concentrations in plasma as putative neurobiological modulators of interindividual variability in pain responses and possibly nocebo hyperalgesia (63–65). To enable analyses of the composition of the microbiome, participants provide a stool sample prior to study day 1.

#### Psychophysiology

2.5.5.

Electrodermal activity (EDA) is continuously recorded during all pain stimulation phases, and skin conductance responses (SCR) to pain-predictive visual cues with a latency of 1 s and until pain onset will be analyzed. The respective peak amplitude during this time interval will be extracted as a proxy of sympathetic nervous system activation reflecting conditioned pain-related fear during pain anticipation, which is a complementary assessment of conditioned responses reflected by analysis of conditioned changes in cue valence (see section 2.5.2) (66). The assessment of conditioned changes in SCR in combination with behavioral responses to conditioned pain-predictive cues builds on our earlier pain-related conditioning studies implementing visceral pain signaled by conditioned visual cues similar to those implemented herein [e.g., (41, 67)].

Heart rate variability analyses will be accomplished over the entire duration of each pain stimulation phase as a measure of stress-related cardiac autonomic regulation (68), based on a continuous one-channel electrocardiogram (ECG) recording. R-peaks of the QRS complexes will be identified to estimate the normal-to-normal (NN) intervals between adjacent QRS complexes resulting from sinus node depolarizations. Standard deviations of NN intervals (SDNN) and the percentage of adjacent NN with a variability of more than 50 ms (pNN50) will be calculated as time-domain parameters reflecting vagally-mediated variations in HRV, along with HF/LF ratio for sympathovagal balance.

Myoelectric activity generated by smooth muscles of the stomach, as can be measured non-invasively with the electrogastrogram (EGG) (69), is reportedly sensitive to stress and emotional arousal in animals and humans (70) and has been shown altered during rectal distension in dogs (71). The EGG has been used in several placebo studies accomplished in the context of nausea [e.g., (72, 73)], or to assess effects of treatment suggestions regarding gastric activity (58, 74–76) in humans, but it has not been applied in the context of acute pain. To explore the EGG as a novel and possibly sensitive measure of nocebo effects relevant to pain, continuous EGG recordings are accomplished in each pain stimulation phase. To acquire data during a phase in which no painful stimuli are implemented, prior to the *Test-2 Phase* on study day 2, a 10-min recording is acquired without any pain stimulation, at the same time serving as habituation phase for possible arousal induced by the experimental set-up. Spectral signatures will be analyzed with respect to power and amplitudes to obtain instability coefficients (IC) reflecting the variability of slow wave activity, the regularity of slow wave activity, the percentage of gastric arrhythmias together with frequency ranges for normal, bradygastric, and tachygastric activity as putative correlates of stress and arousal induced by negative treatment expectations and differences between groups in overall pain responses.

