As primary outcomes, changes in perceived pain intensity and pain unpleasantness will be assessed based on testing for interaction effects and planned group comparisons regarding changes from *Baseline* to the *Test-1 Phase* within each pain modality (study aims 2 and 3). Group differences between pain modalities will be tested based on analysis of delta scores (i.e., changes in visceral > somatic pain responses) (aim 4). Secondary pain-related outcome measures, also tested based on changes from *Baseline* to the *Test-1 Phase* within and between pain modalities, include pain-related expectations (study aim 1), pain recall, and desire to avoid pain. Secondary outcomes related to fear and stress are measured using behavioral, neuroendocrine, and psychophysiological responses, relevant particularly to study aim 6. Responses to pain-predictive cues, i.e., change in cue valence rating and in skin conductance responses, are tested for each pain modality and based on the same experimental phases as for pain-related measures. For neuroendocrine measures, we plan to compare groups with respect to changes from Baseline to subsequent sampling time points. Similarly, group comparisons of differences in heart rate variability and electrogastrogram will be based on analyses of the entire pain stimulation phases (for details, see section 2.4.2). Please note that analyses are planned in two separate steps. Initially, analyses of results of study day 1 will be accomplished. In a second step, analyses comparing data from study day 1 and day 2 (i.e., *Test-1 Phase* vs. *Test-2 Phase*) will be accomplished to explore the possible persistence of nocebo effects over time upon re-exposure to pain stimuli 1 week later (study aim 5). Mediation analyses will be accomplished for aim 1.

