
#### Pain stimulation phases

2.4.2.

The selected objective pain stimulation intensities are applied as follows in the pain stimulation phases: All phases (i.e., *Baseline*, *Test-1*, *Test-2*) are identical, comprising a pseudorandomized series of a total of 12 stimuli (6 visceral, 6 somatic). Of note, the *Experience Phase* is distinctly different in groups randomized to a negative experience which is operationalized by surreptitiously increased thermal pain to the predetermined intensity of VAS 80 mm (see below). Pain stimulus durations are 20 s each, followed by VAS capturing perceptual responses after each stimulus as well as at the end of the series. The order of stimuli is pseudorandomized. To avoid order effects of starting the series with a stimulus from one pain modality, the series starts with either a visceral or a somatic pain stimulus. Additionally, the sequences are programmed to avoid an order containing more than two pain stimuli from the same modality. All pain stimuli are visually cued as a measure of conditioned pain-related fear, and the assignment of a specific cue (i.e., geometric symbol) to a pain modality is counterbalanced. Pain-predictive visual cues appear on a screen 7 s before the pain stimulus, ending at the same time as the pain stimulus (delay conditioning). Total duration of each pain stimulation phase including all digitized ratings is 1,150 s (= 19.17 min). Digital ratings are presented for 12 s, and a fixation cross is shown on the screen in-between stimuli.

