#### Aim 2: to test the effects of negative treatment expectations induced by instruction and/or experience on subjective and objective responses to acute visceral and somatic pain stimuli

3.1.2.

Regarding perceived pain intensity and unpleasantness as main outcomes, we expect that both negative instruction as well as negative experience will result in hyperalgesia for both pain modalities, i.e., greater pain intensity and unpleasantness ratings during the *Test-1 Phase* vs. *Baseline* in experimental groups “Control-Negative” and “Negative-Control” when compared to the group “Control–Control.” Of note, the bars depicting expected results (Figure 4) indicate a similar magnitude of nocebo effect for the groups “Control-Negative” and “Negative-Control.” In other words, we assume in this visualization that the efficacy or impact of instruction and experience will be comparable. It should be stressed, however, that there is no prior evidence testing such an assumption in similar experimental approaches, and it will be interesting to reveal whether the impact of instruction vs. experience is indeed comparable as a basis for translation into practice. If, for example, the impact of negative experience is more “powerful” in terms of inducing sustained nocebo effects when compared to instruction, this will inform strategic and conceptual developments aiming to minimize nocebo effects in clinical practice. Further, we anticipate that the negative experience of objectively increased thermal pain will impact on the perceptual response also to visceral pain (e.g., via generalization and/or cognitive attribution effects, as explained above), exerting an impact also on both pain modalities during the *Test-1 Phase*. Regarding objective measures related to pain, as secondary outcomes, we will explore group differences in psychophysiological responses expecting greater sympathetic activation reflected by differences in HRV and EGG measures in the “Control-Negative” and “Negative-Control” when compared to the group “Control–Control.”

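### SDNN over the whole pain phase is labelled a vagal index, but it is total variability and includes heart-rate shifts evoked by the 12 stimuli, so it can differ between groups without any vagal difference

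*Protocol article*

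**What the plan says.** Section 2.5.5 (Psychophysiology) fixes three things for heart rate variability.

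- **Window:** "Heart rate variability analyses will be accomplished over the entire duration of each pain stimulation phase". Section 2.2 repeats it for the group comparisons: "group comparisons of differences in heart rate variability and electrogastrogram will be based on analyses of the entire pain stimulation phases".
- **Parameters:** "Standard deviations of NN intervals (SDNN) and the percentage of adjacent NN with a variability of more than 50 ms (pNN50", the latter abbreviation closing the definition of the second parameter.
- **Meaning:** both "will be calculated as time-domain parameters reflecting vagally-mediated variations in HRV, along with HF/LF ratio for sympathovagal balance".

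Section 2.4.2 describes what the window contains. The Baseline and both Test Phases are identical, "comprising a pseudorandomized series of a total of 12 stimuli (6 visceral, 6 somatic" stimuli in number, and "Pain stimulus durations are 20 s each". On length: "Total duration of each pain stimulation phase including all digitized ratings is 1,150 s".

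Section 3.1.2 (Aim 2) gives the anticipated result for the groups with a single manipulation against the control group, "expecting greater sympathetic activation reflected by differences in HRV and EGG measures", and places these measures among the secondary outcomes to be explored. Section 2.4.4 adds that in the Experience Phase the thermal stimulus is raised to the level calibrated to VAS 80 mm in the negative-experience groups only.

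**The concern.** The article gives one physiological meaning to two statistics that measure different things. pNN50 looks only at differences between neighbouring intervals. SDNN, as the article itself defines it, takes the spread of all intervals in the window, so it picks up any change in heart rate, fast or slow, vagal or not. The window here is full of deliberate perturbations. A shift of the NN interval during a stimulus and its return afterwards add variance to SDNN. Because the shift enters as a square, this holds whether the heart speeds up or slows down.

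An evoked response of the same size in every group would do little harm to a comparison of changes. The difficulty arises when the response differs by group. That can happen if negative expectation amplifies the response to pain, and it is especially plausible in the Experience Phase, where the heat stimulus itself differs by design. A group difference in SDNN could then be reported as a difference in vagal regulation when it reflects only a larger evoked heart-rate response. At stake is the autonomic interpretation under Aims 2 and 6.

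**Working it through.** **Inputs from the article.** Phase length 1,150 s; 12 stimuli; 20 s each (section 2.4.2). The stated conversion reproduces: 1,150 / 60 = 19.17 min.

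**Inputs assumed, because the article gives none.** Background SD of NN intervals, s0: 30, 50 or 70 ms. Mean NN shift during a stimulus, A: 20 to 120 ms overall, with 20, 60 and 90 ms shown below.

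**Step 1. Share of the window under stimulation.** p = 12 × 20 / 1,150 = 0.2087.

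**Step 2. Variance added to SDNN.** Treating the evoked shift as an on/off component independent of the background:

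SDNN² = s0² + A²·p·(1 − p), with p·(1 − p) = 0.2087 × 0.7913 = 0.1651.

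The added variance is 0.1651 × 20² = 66 for A = 20 ms, 0.1651 × 60² = 594 for 60 ms, and 0.1651 × 90² = 1,337 for 90 ms.

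**Step 3. SDNN under each assumption.**

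| s0 (ms) | SDNN, A = 20 | change vs none | SDNN, A = 60 | SDNN, A = 90 | 90 vs 60 |
|---|---|---|---|---|---|
| 30 | 31.1 | +3.6% | 38.7 | 47.3 | +22% |
| 50 | 50.7 | +1.3% | 55.6 | 61.9 | +11% |
| 70 | 70.5 | +0.7% | 74.1 | 79.0 | +7% |

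In this table the background, and with it any vagal component, is the same in every column. The whole difference comes from the evoked response.

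**Step 4. Does pNN50 behave the same way?** A beat-by-beat simulation of one phase assumed mean NN 850 ms, respiratory modulation with SD 35 ms at 0.25 Hz, slow modulation with SD 25 ms at 0.1 Hz, random SD 10 ms, and evoked shortening with a 4 s time constant (20 runs per setting).

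| Respiratory SD (ms) | A (ms) | SDNN (ms) | pNN50 (%) | RMSSD (ms) |
|---|---|---|---|---|
| 35 | 0 | 44.2 | 35.7 | 47.4 |
| 35 | 40 | 46.4 | 35.6 | 47.1 |
| 35 | 80 | 52.8 | 34.7 | 46.7 |
| 28 | 40 | 41.5 | 22.9 | 39.5 |
| 28 | 80 | 48.4 | 22.2 | 39.2 |

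With respiratory modulation unchanged at 35 ms, raising A from 0 to 80 ms lifts SDNN from 44.2 to 52.8 ms, while pNN50 and RMSSD barely move.

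**Step 5. Can a true vagal fall be hidden?** Compare row 2 with row 5. Respiratory modulation falls by 20% (35 to 28 ms) and the evoked shift doubles (40 to 80 ms). SDNN goes up, 46.4 to 48.4 ms, and pNN50 goes down, 35.6% to 22.2%. So the two indices can part company, but in this example only with a doubled evoked response. In the closed form, with s0 = 50 ms and 60 ms in controls, hiding a 10% fall in background SD (50 to 45 ms) needs A = √[(2,500 + 594 − 2,025) / 0.1651] ≈ 80 ms, a response one third larger. The article gives no figure that would support or exclude either case.

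**The case against.** The best case for the plan has five parts.

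- **Size.** Nothing in the article says how large, or in which direction, the evoked heart-rate response is. A figure near 20% needs a low background SD and a response half as large again in one group. This stands: only a range can be given, and for a 20 ms shift it is negligible.
- **Shared component.** All groups receive painful stimuli, Baseline and Test intensities are identical, and groups are compared on differences across phases. A common evoked component largely drops out. This stands for a common component; it does not help where the response differs by group.
- **Reversal.** A reader might infer that a stronger pain response will appear as greater vagal activity and so cancel or overturn the hypothesis. The documents do not support that. Section 3.1.2 predicts greater sympathetic activation without a direction for each index, and nowhere says that a higher SDNN will be read as evidence against it. That nocebo hyperalgesia produces larger evoked heart-rate responses is a plausible inference, not a statement in the article.
- **Detail left to a fuller plan.** Detrending, segmenting and expected directions may sit in a document not shown, and their absence is no fault here. This stands. But the window and the vagal label are both written down, and it is the label that is wrong.
- **Reach.** HRV is secondary and exploratory, pNN50 is already planned, and a divergence between the two would be visible. This stands, and it limits the weight of the point. It does not repair the label, because the article offers no basis for deciding which of two discordant vagal indices to believe.

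**Conclusion.** The point holds as one of interpretation. SDNN over the entire pain phase is total NN variability, and describing it with pNN50 as vagally mediated is wrong as written, whatever the evoked amplitude. A group difference in SDNN can arise from a difference in evoked response alone, most plainly in the Experience Phase.

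The size cannot be settled from the documents. Under assumed background SDs of 30 to 70 ms, it runs from about 22% down to 7% for a 60 versus 90 ms contrast, and is about 1–4% for a 20 ms shift against none. These figures rest on an on/off shift that is independent of the background. Masking or reversal of a true vagal change is arithmetically possible under chosen values but is not shown for this study. No primary result is affected: pain intensity and unpleasantness do not depend on it.

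**What to change.** In section 2.5.5, or in the analysis plan that implements it:

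1. Describe whole-phase SDNN as total variability and state that it is not used to infer vagal activity.
2. Base vagal inference on pNN50, with RMSSD or HF power taken from the same recording.
3. If SDNN is kept as an autonomic outcome, compute it on the segments between stimuli, or after removing the stimulus-evoked heart-rate response.

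The cost is a change of wording and minor extra processing of an ECG that is already recorded continuously. No study procedure changes. The article describes the study as ongoing with its analyses still planned, so the change can be made before the data are analysed.

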#### Patient-provider communication

2.5.6.

To elucidate facets related to patient-provider relationship and communication, the duration (minutes) of physician-participant communication is recorded, and participants rate perceived warmth and competence of the study physician with 6 items for warmth and competence (77), respectively, at the end of the first study day. Each item is rated on a 5-point scale from 1 (not at all) to 5 (extremely). These ratings capturing the participants’ perspective are complemented by an adapted version of the scale that is completed by the physician who rates the patient/participant on the same dimensions. Items were minimally adjusted for relevant content, and comprise the adjectives intelligent, attentive, anxious, nervous, excited, tense, suspicious, depressed/pessimistic.

#### Additional measures

2.5.7.

In addition to subproject-specific procedures and measures, detailed above, the central projects of the CRC coordinate and administrate standardized assessment of additional measures from all human participants. These include (1) assessment of structural and functional brain connectivity measured at rest in every participant prior to the experimental study protocols, i.e., diffusion tensor imaging (DTI) and resting state functional MRI (rsfMRI) using standardized acquisition and analysis protocols; (2) cortisol awakening response (CAR) and salivary alpha amylase (sAA) activity in all participants as markers of HPA-axis and sympathetic activity, respectively, by obtaining saliva samples on two consecutive days immediately after awaking as well as 30 and 45 min after awakening, and (3) the comprehensive questionnaire battery (mentioned above, see section 2.5.1). These measures will serve analyses across projects aiming to identify predictors of expectancy effects, embedded within the larger CRC approach, along with additional psychological trait and state measures related to stress, negative affectivity, and pain.

## Discussion

3.

### Analyses and anticipated results

3.1.

Based on the background and specific aims, we expect the following results based on planned hypotheses-testing as well as on hypothesis-generating analyses of data collected within the NoVis study, analyzed using analysis of variance (ANOVA) and t-tests as primary analysis approach. A symbolic depiction of the expected group differences in the magnitude of nocebo effects in the four experimental groups is provided in Figure 4.

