### Setting, recruitment, and sample

2.1.

This ongoing study is conducted at the University Hospital Essen, University of Duisburg-Essen, Germany, as part of the Collaborative Research Center (CRC) 289 “Treatment Expectation”, funded by the German Research Foundation (Deutsche Forschungsgemeinschaft, DFG). The overall goal of the CRC is to elucidate mechanisms and clinical implications of treatment expectations.^1^ Within the ongoing first funding phase (7/2020–6/2024), research goals are primarily focused on health outcomes relevant to patients with chronic pain and depression. The present study is accomplished as part of subproject A04 (PI: author [name]), which addresses expectancy effects on pain with a unique focus on visceral pain and conditions involving the gut-brain axis. Ethical approval for research within subproject A04, including the present experimental study, was obtained from the ethics committee at University Hospital Essen (19-8897-BO). The study has been registered in the German Registry for Clinical Studies (DRKS: DRKS00024410). All participants sign consent (for details on two versions of consent forms, see section 2.4.3), and receive a financial compensation for their participation, comprising the two study days involving pain testing described herein, as well as additional assessments accomplished as part of the CRC’s central projects (see section 2.5.7).

The recruitment goal is to include a total of *N* = 120 healthy participants in the study. The sample size is based on *a priori* power analysis with G*Power (42) for interaction effects in a repeated measure ANOVA with the factors time and group. Assuming an effect size of *d* = 0.4 for interaction effects, *α* = 0.05, and 1-β = 0.90, the number of volunteers is *N* = 96. To account for possible exclusions or drop-out and to allow stratified recruitment of male and female volunteers, a group size of *N* = 30 subjects per final experimental group is intended.

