### Design and outcomes

2.2.

The study design is visualized in Figure 1, and procedures are described in detail in subsequent sections. The overall idea behind the design is to experimentally create negative treatment expectations through instruction and experience within a treatment context. This is reflected by the key elements of the repeated measures between-subject design containing the between-group factors “treatment instruction” (negative vs. control instruction) and “treatment experience” (negative vs. control experience). To assess the impact of experimental manipulations on outcome measures, subjective and objective responses to a series of visceral and somatic pain stimuli, delivered during several pain stimulation phases, are assessed (repeated factor). Healthy volunteers are randomized into four experimental groups (recruitment goal: *N* = 30 per group). On study day 1, pain thresholding and calibration/matching procedures and a brief pain habituation phase are initially accomplished. This is done to identify individual stimulation intensities for the pain stimulation phases. Several pain stimulation phases are subsequently accomplished (i.e., three on study day 1; one on study day 2), all consisting of a series of individually-calibrated rectal and thermal pain stimuli. After a *Baseline Phase*, all participants receive an i.v. catheter as a salient element of the psychosocial treatment context, with distinct treatment instructions. Briefly, the negative treatment instruction groups are informed that the opioid antagonist naloxone, which amplifies pain, or saline may be administered in a double-blinded manner. Instruction control groups are informed that only saline is administered as part of standardized procedures. In the subsequent *Experience Phase*, thermal pain stimulation intensities are surreptitiously increased in the negative experience groups to create a clearly discernable experience of amplified pain, whereas intensities remain unaltered in the experience control groups. Two *Test Phases* are accomplished, comprising the identical pain stimulation intensities as during *Baseline*. To test short-term effects of expectancy manipulations, the first test phase is accomplished on study day 1 (*Test-1 Phase*). To explore the persistence of effects, another test phase is accomplished 1 week later (*Test-2 Phase*), yet without any of the salient elements of the treatment context (i.e., there is no i.v. and no interaction with the study physician). In all pain stimulation phases, different facets of visceral and somatic pain perception are acquired, along with questionnaires and ratings, psychophysiological recordings, and saliva and blood sampling at various time points (see section 2.5 for details on measures). Note that in order to minimize circadian effects, all experimental testing is accomplished between 13:00 and 17:00 h, with identical starting times for study day 1 and 2 for each participant. Participants are instructed to abstain from physical exercise on the study day, and to omit food and drink (other than water) within 90 min of the scheduled arrival to the laboratory. They are also instructed not to apply body lotion on the abdomen given application of electrodes on the skin.

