#### Randomization and blinding

2.4.5.

Randomization into one of four groups is accomplished using randomizer.org, stratified by sex. Given that expectancy modulations are at the core of the study, this is accomplished by one dedicated staff member who is not otherwise involved in conducting the study and has no contact with participants beyond initial phone or email contacts and the coordination of the initial appointment/visit with the study physician. The group assignment regarding treatment information group is communicated only to the study physician who explains the study goals and procedures based on version A or B of the consent form and delivers all treatment-related information. As the study physician is therefore necessarily unblinded with respect to the group factor “instruction,” she is blinded regarding the group factor “experience.” This is achieved by a distinct and separate communication between the staff member accomplishing randomization and scientific staff administering pain stimuli, who are therefore unblinded with respect to experience. The study physician is not present during accomplishment of pain phases, and therefore remains blinded throughout. Further, participants’ responses to painful stimuli are not affected by the presence of the study physician. Data entry into a database, data preprocessing, and initial analyses will be accomplished prior to unblinding.

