#### Aim 5: to assess the persistence of nocebo effects on responses evoked by a re-exposure to pain stimuli 1 week later

3.1.5.

We expect sustained effects of expectancy manipulations accomplished on study day 1, which we interrogate based on group comparisons of the *Test-2 Phase*, as well as based on analyses of change scores from the *Test-1* Phase to the *Test-2 Phase*. We anticipate that groups with negative instructions and/or negative experience will expect greater pain on study day 2, i.e., prior to the *Test-2 Phase*, even though elements of the treatment context, such as an i.v. line, will not be present on that day. If we indeed can show such effects, this would be an important finding toward explaining how nocebo effects may be maintained in clinical reality over time and repeated symptom experiences. Given our considerations about differences between pain modalities, especially the putatively greater psychological modulation of visceral pain, we expect sustained effects to be enhanced for the visceral pain modality. We will focus on elucidating modality-specific facets of pain recall, aiming to further elucidate the notion of a memory bias for visceral pain, expanding on our previous work (84) and the notion that visceral pain-related fear memories may be particularly resistant to extinction (41).

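### The primary change-score ANOVA and t-tests are valid but give up precision: adjusting for the Baseline rating and for sex, both already collected, would help, mainly for unpleasantness

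*Protocol article*

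**What the plan says.** Section 3.1 of the protocol article says that the data are "analyzed using analysis of variance (ANOVA) and t-tests as primary analysis approach". Section 2.2 defines the primary test: "changes in perceived pain intensity and pain unpleasantness will be assessed based on testing for interaction effects and planned group comparisons regarding changes from". The change meant there runs from Baseline to Test-1, within each pain modality. Section 2.1 sizes the trial for "interaction effects in a repeated measure ANOVA with the factors time and group". With two phases, the time x group interaction is the same test as a one-way ANOVA on raw change.

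On sex, section 2.4.5 says: "Randomization into one of four groups is accomplished using randomizer.org, stratified by sex". In section 3.2 sex appears only in exploratory and predictor analyses. No section names sex or the Baseline rating as a term in the primary model. The control variables in section 2.5.1 are questionnaire data, and the statistical control mentioned in section 3.2 concerns habituation.

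For Aim 4, section 2.2 plans delta scores between modalities. For Aim 5, section 3.1.5 says: "We expect sustained effects of expectancy manipulations accomplished on study day 1, which we interrogate based on group comparisons of the". The phase compared there is Test-2, and the section adds change from Test-1 to Test-2. Baseline is not used in either Aim 5 analysis.

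**The concern.** A change score subtracts the whole Baseline rating, so it sets the Baseline slope at 1 whatever the data show. If the correlation between Baseline and Test-1 is imperfect, that usually subtracts too much, and Baseline noise enters the outcome. Regression on Baseline estimates the slope instead. Stratifying by sex balances sex across groups, but the analysis gains from that balance only if sex is in the model; otherwise any variance due to sex stays in the error term.

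What is at stake is the width of the intervals for the primary contrasts, above all the combination of instruction and experience, which section 3.1.3 calls the most crucial aspect of the study.

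For Aim 5, the Test-2 comparison leaves Baseline information unused. Change from Test-1 to Test-2 describes how far an effect has decayed, not how much of it remains.

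**Working it through.** **Inputs from section 2.1 and section 2.2.** "Assuming an effect size of *d* = 0.4 for interaction effects, *α* = 0.05, and 1-β = 0.90, the number of volunteers is *N* = 96". "Healthy volunteers are randomized into four experimental groups (recruitment goal: *N* = 30 per group"). The correlation between phases and the SDs are not stated.

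**Reproducing N = 96.** Take f = d/2 = 0.2, k = 4 groups, m = 2 phases and an assumed correlation rho = 0.5.
- Noncentrality = N·m·f²/(1 − rho) = 96 × 2 × 0.04/0.5 = 15.36, with 3 and 92 degrees of freedom.
- Power is 0.912 at N = 96 and 0.898 at N = 92, so 96 is reproduced.
- With the same four groups and two phases, rho = 0.3 would need 128 and rho = 0.7 would need 60.

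**Baseline adjustment in general.** Write s0 and s1 for the Baseline and Test-1 SDs.
- Change-score variance: s0² + s1² − 2·rho·s0·s1.
- ANCOVA residual variance: s1²(1 − rho²).
- Difference: (s0 − rho·s1)². This is never negative, so apart from the degrees of freedom ANCOVA does not lose precision.

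**Equal SDs.** The variance ratio is (1 − rho²)/[2(1 − rho)] = (1 + rho)/2.

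| rho | variance ratio | CI width ratio |
|---|---|---|
| 0.3 | 0.65 | 0.81 |
| 0.5 | 0.75 | 0.87 |
| 0.7 | 0.85 | 0.92 |

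At rho = 0.5, power of the four-group test on the planning effect rises from 0.912 to 0.973 at N = 96, and from 0.964 to 0.993 at N = 120. For single contrasts, assume a difference of 0.4 SD of the rating, 30 per group and rho = 0.5:
- pairwise comparison: 0.33 to 0.42;
- instruction x experience: 0.19 to 0.24;
- main effect: 0.58 to 0.71.

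**Smaller Baseline SD, as calibration may produce for intensity.** Assume s0 = 8 mm and s1 = 15 mm.
- rho = 0.3: 225 × 0.91/(64 + 225 − 72) = 204.75/217 = 0.94.
- rho = 0.5: 225 × 0.75/(64 + 225 − 120) = 168.75/169 = 0.999.
- rho = 0.7: 225 × 0.51/(64 + 225 − 168) = 114.75/121 = 0.95.

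The gain is then 0 to 6%.

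**Sex.** Simulation with 4 × 30, half of each sex, 4000 runs; the sex effect on change is in residual SD units.

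| sex effect | type I error, sex omitted | power, omitted v included |
|---|---|---|
| 0 | 0.052 | 0.90 v 0.89 |
| 0.4 SD | 0.041 | 0.88 v 0.90 |
| 0.8 SD | 0.029 | 0.84 v 0.90 |

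Omitting sex makes the test conservative if sex predicts change, and makes no material difference if it does not.

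**Test-2.** Against an unadjusted Test-2 comparison, adjustment for Baseline multiplies the variance by 1 − rho²: 0.91, 0.75 and 0.51 at rho = 0.3, 0.5 and 0.7.

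**The case against.** The strongest reply is that nothing here is an error. Sections 2.1, 2.2 and 3.1 agree with each other, the test is valid under randomisation, and a condensed article need not list covariates. The validity point stands: this is about efficiency. But the article does commit to a method and a primary contrast, and adjustment differs from both, so the suggestion is properly made.

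The second reply also stands in part. Section 2.4.3 places randomisation and the two consent forms before Baseline, so Baseline may already carry some instruction effect. If instruction shifts Baseline by delta and the slope is b, the ANCOVA contrast differs from the change-score contrast by (1 − b)·delta. With assumed values of 5 mm and 0.5, that is 2.5 mm. The adjustment therefore has a cost for the instruction factor.

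Several stronger readings are tempting, and the documents do not support them:
- **Regression to the mean from calibration.** A reader might infer that Baseline ratings were themselves steered to 40–60 mm. Section 2.4.1 steers the calibration, matching and habituation ratings; Baseline is a fresh series of six stimuli per modality.
- **A gain equal to 160 participants instead of 120.** This is 120/0.75. It needs equal SDs and rho = 0.5, which is back-calculated from the sample size and says nothing about the data.
- **Sex ruled out of the model.** Section 3.2 says subsamples are too small for conclusions about sex differences. That does not exclude a main-effect term. Stable sex differences in rating level also cancel in a change score.
- **A non-significant change read as persistence.** Section 3.1.5 lists the Test-2 group comparison first and nowhere says this. Section 2.2 calls the step exploratory.

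**Conclusion.** The point holds as an improvement in efficiency, not as a flaw in validity. The planned primary test leaves precision unused because it fixes the Baseline slope at 1 and omits the stratification factor. With equal SDs, adjustment would remove 35%, 25% or 15% of the change-score variance at rho = 0.3, 0.5 or 0.7. These figures fit unpleasantness better, since section 2.5.3 notes that it is not adjusted during calibration. For intensity the gain may be negligible. All of this rests on assumed correlations and SDs. The benefit of including sex depends on whether sex predicts change. For Aim 5, adjustment sharpens a Test-2 comparison that is already planned, and the change score needs a clear statement of what it can show.

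**What to change.** Before unblinding, specify the following.

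1. **Primary outcomes (Aims 2 and 3).** For each outcome and modality: Test-1 mean rating = instruction + experience + instruction x experience + same-modality Baseline mean + sex. Take the planned within-modality comparisons as contrasts of this model, with 95% CIs.
2. **Aim 4.** Fit the same model to the visceral-minus-somatic Test-1 difference, with the Baseline difference and sex as covariates. Separate models per modality cannot supply this contrast with a valid standard error.
3. **Aim 5.** Fit the same model to the Test-2 rating and report effects with 95% CIs next to those at Test-1. Keep Test-1-to-Test-2 change as a description of decay, and state that a non-significant change is not evidence of persistence.
4. **Sensitivity.** Report the planned change-score contrast and the unadjusted Test-1 contrast, because Baseline follows the consent-stage instruction. For a slope between 0 and 1, the ANCOVA estimate lies between the two, so a wide gap would show that Baseline had shifted.

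The cost is two degrees of freedom, plus care in interpreting the instruction factor. No new data, participants or procedures are needed.
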